# Effectiveness and acceptability of two insertable device models for non-surgical management of obstetric fistula: protocol for a hybrid type I randomized crossover trial

**DOI:** 10.1186/s12905-025-03823-y

**Published:** 2025-07-04

**Keywords:** Vesicovaginal fistula, Incontinence management, Insertable device, Effectiveness, Acceptability, Stigma, Quality of life

## Abstract

**Background:**

Obstetric fistula is a traumatic and stigmatized maternal morbidity often resulting in severe urinary and fecal incontinence. Women with fistula face multi-level barriers to surgical repair culminating in delays. Unfortunately, no acceptable temporizing measures to contain incontinence of urine exists. An insertable vaginal cup, alone or connected to a leg bag, has potential for improving incontinence management for women awaiting surgery or those whom surgery was unsuccessful, but effectiveness and acceptability are unknown.

**Methods:**

We describe a four-year clinical trial and nested qualitative study to examine the effectiveness and acceptability of an insertable vaginal cup to manage fistula urinary incontinence and understand fistula management costs. Two intervention models will be compared to a control: (1) vaginal cup (‘cup’), and (2) vaginal cup attached via tubing to a leg-secured urine collection bag (‘cup+’). Using a cross-over design, up to 100 participants will be block randomized to one of two sequences of leaking freely (no intervention), cup, and cup + at four fistula centers in Ghana and Kenya and observed for four days (400 total observations). Data will be captured through interviewer-administered survey, clinical exam and checklist. After clinic-based assessment, participants are individually randomized for cup or cup + for home use for up to 3 months and surveyed monthly. Effectiveness will be evaluated through quantitative comparison of urinary leakage (6 h and 24 h) and patient-reported quality of life (1–3 months) between cup, cup+, and leaking freely. Acceptability will be assessed quantitatively (1–3 months) and via in-depth interview among selected trial participants (*n* ~ 30) and potential implementers (*n* ~ 20).

**Discussion:**

This implementation study will inform the effectiveness and acceptability of the cup and cup + interventions as temporizing management strategies for fistula urinary incontinence. If the cup/cup + is effective and acceptable, this study will provide insight for future trials and cost-effective assessments in settings where fistula is prevalent. Expanding the evidence base on non-surgical temporizing management options will inform comprehensive fistula care through tertiary prevention and is likely to reduce vulnerability to stigma and improve economic opportunity and quality of life.

**Trial registrations and dates:**

ClinicalTrials.gov NCT05444504 (Date of registration: July 6, 2022). Pan African Clinical Trial Registry 202,209,466,217,416 (Date of registration: 9/22/2022). Ghana FDA Certificate FDA/CT/231 (Date of approval: 3/30/2023).

## Background

Prevalence estimates suggest that more than 500,000 women and girls live with the birth injury obstetric fistula, primarily in lower-resource settings [1, 2] While fistula repair capacity is increasing globally, [3–5] with as many as 100,000 annual incident cases,^1^, ^2^ current surgical capacity is inadequate and many women face surgical treatment delays [6–8]. For example, in Ghana, where fistula incidence is estimated at ~ 1 per 1000 births, [9] impacting ~ 1,350 women annually, annual repair capacity is < 150; thus, Ghanaian women report living with fistula for a median of eight years prior to repair (Interquartile Range (IQR): 4–14) [10]. Similar substantial care delays are observed in Kenya, where women have been reported to wait on average 8.1 years (SD 9.2) for surgery. The substantial and persistent discrepancy between surgical capacity and new fistula cases in Ghana, Kenya, and in other countries where fistula is prevalent leaves a significant backlog of women in need of care and facing multi-level barriers to timely access to surgical fistula management.

Chronic urine leakage from obstetric fistula results in stigma, including discrimination, social isolation, and shame causing mental health and economic consequences [11–14] that significantly reduce quality of life [15–21]. Women with fistula cope with urine leakage with low-cost materials, however, with challenges [22–25]. In many settings where obstetric fistula occurs, diapers or sanitary pads are prohibitively expensive or unavailable; thus women use absorptive fabrics that hold urine against the skin, causing severe irritation, and require frequent washing [26]. Effective options for self-management of fistula leakage are inaccessible for most. Thus, increasing accessibility to safe, low-cost tools are needed, including acceptable, non-surgical innovations to manage fistula urinary incontinence until timely access to surgical fistula repair is assured.

Insertable devices, or technologies that reside within the body, have many applications to improve women’s health and quality of life [27, 28]. An insertable vaginal cup is an acceptable, safe, and effective solution for preventing leakage of menstrual blood and eliminating odor among women and girls worldwide including settings where fistula is prevalent [29–33]. Incidental findings in case reports suggest the utility of the menstrual cup for control of urine leakage in women with fistula [34–36] however, no systematic evaluation of the effectiveness of the cup within a fistula-endemic setting has been conducted. The cup is durable, reusable, and low-cost in addition to being concealable to prevent additional stigma burden. It sits low in the vagina, and thus is suitable for collecting leakage for selected vesicovaginal fistulas (VVF). Urine is emptied from the cup after removal or via valve release while inserted.

Our collaborative team of physicians and researchers from University of Ghana and New York University were the first to systematically evaluate efficacy and acceptability of an insertablevaginal cup for short-term vesicovaginal fistula management at a health facility in Ghana within a feasibility study [37, 38]. The mean leakage reduction with cup use over two hours was 61% (95% CI: 35.9–86.2), a difference users perceived in reduced wetness (10/11), including a 64% mean leakage reduction among the five participants with previous surgical attempts. Acceptability was high; women could easily insert (8/11), remove (8/11), and comfortably wear (11/11) the cup, and most (10/11) would recommend it. No adverse effects attributable to use of the cup were observed on gynecological exam. The data collection tools (e.g., pad test and questionnaire on perceived reduction of leakage and acceptability) were appropriate and easily implemented in the local context. These findings suggested robust evaluation of short and long-term effectiveness is warranted along with continued evaluation of user acceptability, including how use of the cup could supplement or replace existing coping strategies [4, 39, 40].

Results of the feasibility study suggested two key design modifications to target an insertable device for fistula management [41]. A valve would allow the user to empty the cup without removing it from the vagina, thus reducing the emptying frequency (Table 1). Results also suggested that users may benefit from greater storage capacity through connecting the valved cup via rubber tubing to a drainage bag attached to the leg by soft elastic bands and concealed under clothing. The larger capacity of the drainage bag (540 ml) could allow users to empty the urine less frequently compared to the cup alone (35 ml) without worrying about leakage. This would be beneficial when women lack immediate access to water and a safe, private space to empty and wash their cup. Women coping with fistula already maintain strict hygiene practices, thus additional cleaning and hygiene needs are not concerning [42, 43]. The cup alone may be more appropriate for shorter duration or among women with less severe leakage while cup plus leg bag (cup+) may be more appropriate for longer duration (e.g., traveling greater distance without latrine access) or among women with more severe leakage. Acceptability could vary by model, change over time and is dependent on multiple factors and contexts.

**Table 1 Tab1:**
[figure not shown]
Description of the cup and cup + Intervention models

Cost is an important implementation outcome for this and any fistula management intervention. Although qualitative studies have suggested women devote significant time and effort to non-surgical fistula management, [14, 26, 44, 45] no rigorous quantification of material and opportunity costs exists. As such, the economic burden of fistula is not well understood, which limits valid estimation of the benefits of fistula interventions. Micro-costing of non-surgical management is needed to quantify the burden of managing fistula urine leakage to comprehensively characterize the social and economic impact of any fistula management intervention. Cost-effectiveness of fistula surgery has been previously evaluated in Uganda, showing that for a hypothetical 20-year-old woman with fistula, surgery was estimated to decrease the lifetime disability burden from 8.53 DALYs to 1.51 DALYs, yielding a cost of $54 per DALY averted [46]. However, cost comparisons and cost-effectiveness analysis have yet to be conducted between methods of self-management of fistula. Various aspects contribute to financial and economic cost of fistula management; 47] valved menstrual cups that would meet the needs identified in our prior research are now available (cost of $4.50 per unit) and tubings with leg bags are readily available (combined cost of $6.10 per unit).

As acceptability, appropriateness, and other implementation barriers have been previously identified when implementing evidence-based tools for incontinence management, [48, 49] menstrual hygiene management, [31] and surgical management of fistula, [50, 51] contextualizing implementation while evaluating the impact of the cup and cup + is critical. Therefore, this study will evaluate the effectiveness and acceptability of a valved vaginal cup and a valved vaginal cup with tubing for non-surgical management of VVF, estimate fistula-related management costs, and understand the implementation context for the cups. Importantly, the comparison for effectiveness outcomes is not surgery but free leakage. Identification of effectiveness and acceptability for either intervention model could influence a shift in clinical fistula management practice paradigms. Qualitative findings from community assessment of the cup and cup + among users and fistula stakeholder interviews will help explain quantitative results regarding efficacy, effectiveness, or adherence.

We hypothesize that limits to the cup/cup + effectiveness for fistula incontinence management are likely to be attributable to acceptability and adherence [52]. While the use of cup/cup + for fistula incontinence management is novel, cups and other intra-vaginal devices for menstrual management, [53 contraception,^54^] and prevention of sexually transmitted infection [55, 56] are used when available and accessible and have been found to be acceptable throughout sub-Saharan Africa [57] To support a multi-dimensional understanding of both user and implementer acceptability and cost of cup/cup+, use of behavioral frameworks like the Theoretical Framework of Acceptability [58] can help identify how acceptability shapes user adherence and uptake and guide identification of optimal user and implementer characteristics. Our theory-oriented approach will inform generalizability of our effectiveness findings, provide an understanding of context, and help identify implementation strategies that may improve implementation outcomes, such as acceptability, appropriateness, and cost.

## Methods

### Study design

This hybrid type I randomized crossover phase III clinical trial and nested qualitative [59] study employing a concurrent mixed-methods approach (Fig. 1) [60] seeks to longitudinally quantify the effectiveness and comparative effectiveness of the cup and cup + to manage vesicovaginal fistula urinary incontinence (Aim 1) among up to 100 women in Ghana and Kenya who have not yet accessed treatment or have failed surgical repair, examine acceptability of the cup and cup+ (Aim 2), and estimate the material and opportunity costs of non-surgical fistula management (Aim 3).

**Fig. 1 Fig1:**
[figure not shown]
Mixed-methods study diagram

At the health facility, participants will first undergo baseline assessment of leaking freely (six hours). Participants will be block randomized within a crossover design [61] to varying sequences of leaking freely, using the cup, and using the cup+ (Fig. 2). During clinic-based assessment, the study will quantitatively evaluate short-term comparative efficacy (at six hours) between the cup and the cup + and assess medium-term comparative effectiveness (at 24 h). Participants will be subsequently individually randomized to take home either the cup or the cup + as part of a community assessment of longer-term effectiveness, including change in quality of life (after one to three months). Preliminary clinic- and community-based assessment results will connect the qualitative phase by informing the qualitative stakeholder interview guide and purposive selection of a sub-sample of purposively selected trial participants, partners, and peers (*n* ~ 30). These individuals will be interviewed for an in-depth understanding of user-cup interactions, acceptability, stigma, and quality of life. We will also begin to qualitatively examine the implementation context for the cup and the cup + as perceived by providers (*n* ~ 20).

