#### Quality of life

Using dependent t-test with 2-tailed, alpha error = 0.05, estimated mean difference of effect between the cup and cup + of 40%, and power 0.85 to avoid type 1 error, required sample size is 59. Estimates of the effect are based on data collected within a longitudinal study of post-surgical fistula repair patients in Uganda, [66] wherein participants were asked about quality of life using the post-repair fistula reintegration measure which is standardized to a range of 0-100 [67]. Participants reported a mean of 36.7 (SD = 19.0) at the time of fistula repair (referring to living with fistula) and a mean of 78.0 (SD = 22.7) at follow up (6 months post-repair), reflecting a mean change of 40.5 (SD 28.1): 54.2 (SD 14.5) among those who were not leaking urine and 13.1 (SD 28.9) among those who continued leaking urine. The cup + is estimated to have a comparable improvement on quality of life as surgical repair, while the cup, based on our observations during our feasibility study [37] and on expert opinion, is estimated to have a smaller effect on quality of life over the long-term (3 months) as it has 1/15th of the capacity for urine storage and thus will need more frequent emptying than the cup+.

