##### Randomization

Participants will be group randomized to one of two groups of varying sequences of 24 h of either leaking freely, cup, or cup+ (Fig. 1). This crossover design uses participants as their own controls, reduces the risk of confounding due to intervention order, and captures two estimates of leaking freely (group 1) and cup (group 2) to assess any sequential differences in leaking variability. Based on the intervention mechanism of effect and lack of carry-over effect, no washout period is required between sequences. As the clinic-based component of the trial will be implemented in small groups prioritizing feasibility and quality control, randomization at the group level is preferred and will be implemented by the study data manager at the time each cohort is recruited using coin toss. The study physician and nurse will enroll participants and inform them of the treatment group for immediate participation.

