##### Data collection

Data will be collected within the clinic-based phase via questionnaire, clinical exam (by a physician), clinical checklist (by nurse/midwife), pad test, and observation (Fig. 1; Table 2). At baseline, a gynecological exam will be carried out as potential participants are being screened and, once enrolled, the baseline questionnaire will be administered. Data will be directly entered into the REDCap mobile app to facilitate data privacy and quality. Next, all participants will be provided disposable pre-weighed adult pads or diapers for the first six hours of each treatment assignment while carrying out typical activities daily living activities on the ward. Six hours was deemed to be a clinically significant amount of time to provide women some relief from their leaking to allow them to engage in social activities or sleep uninterrupted. Additionally, six hours will likely provide those in the cup + assignment the opportunity to fill and then empty their leg bag. Lastly, six hours was deemed logistically feasible for data collectors (i.e., at the start and end of their shift). When assigned to cup or cup+, participants will also insert and wear the respective cups. Women will be encouraged to void ‘normally’ if they sense urgency and instructed to change their diapers as frequently as they see fit when they feel dampness and to deposit the used diapers into a personal plastic Ziplock bag that is then sealed until study staff can record the weight of the wet diapers. At the end of the first six hours of each treatment assignment, the weight of the participant’s assigned dry diapers will be subtracted from that of the wet diapers to calculate the volume of urine leaked, and participants will be asked questions regarding perceived effectiveness. Participants will continue with their assigned treatment until 24 h of use, at which time another questionnaire and a clinical checklist to note any adverse events will be administered by the study physician or nurse/midwife.

**Table 2 Tab2:** Quantitative study measurements, data sources, and timing of assessment

Category	Measure	Data Source^a^	Clinic				Community		
			0h	6h	24h	4d	1m	2m	3m
Outcome variables									
Quality of life ^b,c^	Quality of life (Post-fistula repair reintegration instrument)^*92*^	PS	●				●	●	●
Urine leaked (observed) ^c^	Pad weight; number of pads used, food and fluid intake, voiding	PT, TM		●					

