### Community-based procedures

On the last clinic day, participants will be individually randomized to use of cup or cup + at home for up to three months (see Randomization; Fig. 1) for community-based assessment of the longer-term effectiveness, acceptability of the cup and cup+, and material and opportunity costs to non-surgical fistula management. We will assess perceived change in leakage associated with cup/cup + use, quality of life, acceptability and adherence via survey and clinical checklist administered at one and two months either over the phone as we have done in prior studies [63, 74] or in-person per participant and data collector preference, and semi-structured interview and clinical exam in-person at three months. Participants will be provided with airtime to ensure their ability to contact study personnel.

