##### Quality of life

We will compare mean difference in quality of life score as measured by the post-fistula repair reintegration instrument [83] at 1–3 months compared to baseline using McNemar’s test by intervention and will separately model the trajectory of quality of life across our five assessment points using mixed-effects linear regression analysis of assessment points within individuals. Comparative effectiveness of the cup vs. cup + on quality of life will be assessed by comparing the respective quality of life change using paired t-test. Perceived leakage will be assessed similarly. As we observed a wide variability in baseline leakage in our feasibility study (63.2 ml ± 49.2) [84] and clinical cut points leakage reduction are not established, we will use quality of life estimates to identify a clinically significant leakage reduction. Quantitative measures of *short-term user acceptability* will be described using appropriate distributional statistics and compared between cup vs. cup + using paired t-test (continuous) or McNemar’s test (categorical). Quantitative measures of *long-term acceptability* will be described by cup vs. cup + through modeling their trajectory across community assessment and comparing these statistically using mixed-effects linear regression analysis. In secondary analyses we will assess various potential confounders will for association with the primary outcome variable (% change in volume of urine leaked at 6 h of use) as well as with user acceptability score. A direct relationship will also be assessed between effectiveness (self-perceived change in volume of urine leaked) recorded at 24 h of use and at 1, 2, and 3-month follow-up for both intervention models.

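### The home quality-of-life comparison of cup and cup+ uses a t-test with no covariate, although each woman's clinic pad-test leakage is recorded before her home randomisation and could sharpen it

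*Protocol article*

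**What the plan says.** The home phase is a parallel comparison. Under Community-based procedures: "On the last clinic day, participants will be individually randomized to use of cup or cup + at home for up to three months". Study design says the same in other words: "Participants will be subsequently individually randomized to take home either the cup or the cup", the alternative being cup+.

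Leakage is measured before that point. Study design: "At the health facility, participants will first undergo baseline assessment of leaking freely (six hours"). Data collection adds that women wear "pre-weighed adult pads or diapers for the first six hours of each treatment assignment", and the clinic assignments comprise leaking freely, cup and cup+. A woman who completes the clinic phase therefore has a weighed value under all three conditions before her home device is drawn.

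Under Data analysis, Quality of life, the comparative effect on "quality of life will be assessed by comparing the respective quality of life change using paired t-test". A separate mixed-effects trajectory model is described, with no covariate named. The planned secondary work on confounders concerns six-hour leakage change and the acceptability score, not quality of life. Quality of life is also to be used to find a clinically meaningful leakage reduction, which is not an adjustment.

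The sample size section reports quality-of-life change in a surgical cohort as "54.2 (SD 14.5) among those who were not leaking urine and 13.1 (SD 28.9) among those who continued leaking urine".

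**The concern.** The protocol treats leakage as the route by which a device improves quality of life. It plans from figures in which dry and leaking women differ by 54.2 − 13.1 = 41.1 points. Background also expects severity to matter, saying that cup+ "may be more appropriate for longer duration (e.g., traveling greater distance without latrine access) or among women with more severe leakage". The plan measures leakage before the home randomisation and then leaves it out of the comparison.

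What is at stake is precision. Any variation in quality-of-life change that clinic leakage could explain stays in the error term. The home phase can expect only about 40 women per device, so there is little precision to spare.

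**Working it through.** **Inputs.** Sample size section: overall change 40.5 (SD 28.1); not leaking 54.2 (SD 14.5); still leaking 13.1 (SD 28.9); two-sided alpha 0.05; power 0.85; a difference of 40%; N = 59; up to 100 women; more than 80% retention. Taking 80% of 100 gives 80 women, 40 per arm.

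**1. The plan's own figure.** A paired t-test (exact noncentral t) with a standardised effect of 0.40 has power 0.856 at n = 59 and 0.8496 at n = 58. So 59 is reproduced if 40% means an effect of 0.40, that is 0.40 × 28.1 = 11.2 points. Read as 40 points with SD 28.1, the answer would be 7 pairs.

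**2. Share of variance linked to leaking in the planning cohort.**
- Proportion not leaking: (40.5 − 13.1)/(54.2 − 13.1) = 27.4/41.1 = 0.667
- Between-group variance: 0.667 × 0.333 × 41.1² = 375.4
- Within-group variance: 0.667 × 14.5² + 0.333 × 28.9² = 418.6
- Total: 794.0, SD 28.2 (stated: 28.1)
- Share: 375.4/794.0 = 47.3%

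This concerns dry or leaking status after surgery. It is used below only as a ceiling.

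**3. Precision of the home comparison.** Residual SD = 28.1 × √(1 − R²). The detectable difference is the value giving 85% power in a two-sample noncentral t with 40 per arm and standard error residual SD × √(2/40). R² for the clinic pad tests is not in the documents, so the values below zero-to-ceiling are assumed.

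| R² | Residual SD | Detectable difference, 85% power | Power if the true effect is 0.40 × 28.1 |
|---|---|---|---|
| 0 (as planned, two arms) | 28.1 | 19.1 | 0.42 |
| 0.1 | 26.7 | 18.1 | 0.46 |
| 0.2 | 25.1 | 17.1 | 0.51 |
| 0.3 | 23.5 | 16.0 | 0.56 |
| 0.473 (ceiling) | 20.4 | 13.8 | 0.68 |

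**4. Is chance imbalance a further problem?** At the ceiling, the SD of the arm difference in proportion leaking is √(0.667 × 0.333 × 2/40) = 0.105, worth 0.105 × 41.1 = 4.3 points. The unadjusted standard error is 28.1 × √(2/40) = 6.3 points. The ratio squared, (4.33/6.28)², is 0.475: the same 47% again. Imbalance is already inside the standard error and must not be counted twice.

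**5. Price of the covariates.** Three leakage values plus four sites (three indicators) make six terms. Losing six error degrees of freedom moves the detectable differences by about 0.02 points. Estimating the coefficients also inflates the variance by about (80 − 3)/(80 − 3 − 6) = 77/71 = 1.085, for roughly normal covariates. Break-even is R² = 1 − 71/77 = 0.08 for all six terms together. Allowing for this:
- R² 0.1: 19.1 × √(0.9 × 1.085) = 18.9 points
- R² 0.2: 19.1 × √(0.8 × 1.085) = 17.8 points
- Ceiling: 19.1 × √(0.527 × 1.085) = 14.4 points

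**The case against.** A t-test on change between randomised arms is valid, and an article may leave covariates to a fuller document. The first half stands: this is about efficiency, not validity. The second half does not dispose of the point. The article names a test that cannot carry a covariate and directs its confounder work at other outcomes.

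A reader might infer that clinic leakage explains nearly half the variance in quality-of-life change. The documents do not support that. The 47% comes from a yes/no outcome of surgery, observed at six-month follow-up in another cohort. The trial's covariate is a six-hour weight taken before home randomisation, in women who all enter leaking. No correlation with later quality of life is given.

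A reader might also infer that chance imbalance in leakage biases the result. It does not; step 4 shows it is variance the t-test already counts.

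A third inference would be that the home randomisation is faulty for not being stratified. The article only fails to state stratification: Community-based procedures points to Randomization and Fig. 1, that text describes only the clinic-phase allocation, a coin toss ("randomization at the group level is preferred and will be implemented by the study data manager at the time each cohort is recruited using coin"), and the figure is not shown. Splitting at a median across four sites would also be impractical for at most 100 women enrolled in clusters of 4 to 10.

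The Background remark on severity concerns which women suit which device. That is effect modification, which a main-effect covariate does not address.

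Finally, adjustment does not decide whether the comparison is adequate. If the true difference is 40 points, unadjusted power exceeds 0.99 even with 59 women. If it is 0.40 SD, power with 40 per arm is 0.68 even at the ceiling.

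**Conclusion.** The point holds as a question of precision. The stated comparison is unbiased but leaves out pre-randomisation measurements that the protocol's own reasoning marks as relevant. With 40 per arm and SD 28.1, the detectable difference falls from 19.1 points to 18.1, 17.1 or 13.8 at R² of 0.1, 0.2 or 0.47, before the small price of estimating several covariates. Near R² 0.1 the six-term model gains almost nothing; from about 0.2 upward the gain is useful.

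This assumes 80 women retained in equal arms, the surgical cohort's SD, and an R² that the documents do not give. It makes no claim that the home allocation is wrong.

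The paired form of the t-test is a separate fault in the same sentence, since each woman takes home only one device. Changing it to a two-sample test would still leave leakage unused.

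**What to change.** Replace the home quality-of-life t-test with a between-group regression, or a repeated-measures model, of cup versus cup+. Include as covariates the woman's clinic six-hour leakage leaking freely, on cup and on cup+, plus site.

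Enter both device values for every woman. Using only the value for the device she was assigned would adjust away part of the device effect.

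State in advance the scale for leakage, which value is used where a condition was measured more than once, and a simple rule for missing pad tests, since women may stop any individual clinic assignment.

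The cost is one changed passage in the analysis section, a few degrees of freedom and the variance price in step 5. Averaging the two device values would save one term. No new measurement, visit or participant is needed, and the change should be fixed before comparative home data are examined; 16 women had completed at the time of the article. Stratifying the home randomisation by leakage is optional and not needed for this fix.
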